### Participants and recruitment

We aim to include a total of net 1000 families in the cohort study. Recruitment will take place in two parts.

Part A) A sample of net 800 parents/caregivers of children aged 0–7 year will be included by two regional preventive youth health care providers (CJG Rijnmond and Rivas Zorggroep) in the regions of Rotterdam and Dordrecht, the Netherlands. These preventive youth health care organizations will inform a sample of parents/caregivers of children aged between 15 and 21 months and children aged 5 or 6 years (second grade of primary school) from their registries about the study, and invite them to participate. All invited parents/caregivers will receive project information, an informed consent form and a baseline questionnaire. Parents/caregivers who are willing to participate are requested to return the completed baseline questionnaire and the signed informed consent form to the researchers in a pre-paid envelope or via internet. All parents/caregivers who provide informed consent and a completed questionnaire are enrolled in the study.

Part B) Part B concerns an opportunity sample of net 200 parents/caregivers of children aged 0–7 year who will participate in a parenting intervention during the follow-up period. Preventive youth health care organizations and other providers of parenting support are informed about the study. They are asked to inform parents who participate in interventions about the study. The procedure regarding study information, informed consent and data collection is similar as for the parents in part A. In addition, participants are recruited directly through advertisements on websites about parenting. They will be directed to the digital version of the project information, the informed consent form and the questionnaire. All parents/caregivers who provide informed consent and a completed questionnaire are enrolled in the study.

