### Data collection and measurements

Data will be collected through questionnaires that will be filled out by the primary caregiver of the child at baseline (time of inclusion) and after a follow-up period of twelve months. The questionnaires can be completed on paper or digital through a secured website. All questionnaires consist of valid and evidence-based instruments; details are described below. In the questionnaire, the participants can indicate whether they want support by a professional caregiver; if so, they will be referred accordingly.

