### Outcome measures

The outcomes of this study are variables related to parenting, family life and child development. Unless otherwise specified, measures will be assessed at baseline as well as at follow-up.

General parenting styles and parental practices will be measured using two scales previously described by Wake [26]. The sub scale ‘warmth’ comprises six items from the Child Rearing Questionnaire [27] addressing the frequency of warm affectionate behaviors of parents towards their children. The sub scale ‘control’ includes five items from the National Longitudinal Survey of Children and Youth (Statistics Canada. National Longitudinal Survey of Children), addressing the frequency with which parents set and enforce clear expectations and limits. Items will be rated on 5-point scales, ranging from 1 (never/almost never) to 5 (all the time). The warmth and control sub scales will be used to define four parenting styles: authoritative (high warmth and high control), authoritarian (low warmth and high control), permissive (high warmth and low control), and disengaged (low warmth and low control).

Dysfunctional discipline strategies in parents will be measured with the Parenting Scale (PS) [28]. The PS consists of 30 items. Each item is rated on a seven-point Likert scale, ranging from a high probability to use an effective discipline strategy to a high probability of using ineffective discipline strategies. One item (When my child misbehaves, I spank, slap, grab, or hit my child) will not be assessed in this study, due to perceived invasiveness to parent(s)/caregiver(s). Three subscales will be computed: over-reactivity, laxness and verbosity.

Daily parenting stress will be measured with the Parenting Daily Hassles Scale (PDH) [29, 30]. The measure consists of 20 typical daily events in parenting and parent-child interactions. Parents/caregivers will be asked to rate the frequency of each potential hassle in the previous week on a 4-point scale (rarely, sometimes, a lot, constantly). Additionally, they will rate the intensity of the hassles on a 5-point scale, ranging from 0 (no burden) to 4 (great burden).

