### Received parenting support and use of care

In the baseline questionnaire, the use of various types of care in the previous year by the parent/caregiver, child and/or other children in the family will be assessed, including the general practitioner, medical specialists, psychological help, parenting support and other types of care (18 items). Furthermore, we include 3 items regarding visits to the youth health care centers.

In the follow-up measurement, the use of care will be assessed similarly as in the baseline questionnaire. Additionally, 3 items are included to assess whether parents/caregivers had questions or concerns regarding the upbringing of their child, whether they had been in need for parenting support and whether they have received parenting support during the follow-up period. Visits to youth health care centers, participation in parenting interventions, visits to parenting lectures and other types of parenting support during the last year are assessed by 20 items, including items considering the duration, frequency, character, content and the parents’/caregivers’ appreciation of the received parenting support. Additionally, when available and with permission of participants, data on received parenting support and care regarding parenting during the follow-up period will be collected from electronic files of preventive youth health care organizations.

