### Elements in parenting interventions and other types of support

Elements of the parenting support that were received by parents/caregivers will be identified and coded. For this purpose, we will inventory the guidelines and/or protocols of the interventions that were reported by the parents/caregivers. In this study, content elements (objectives or general themes/principles) and delivery elements are extracted [12]. Delivery elements are operationalized as elements related to what was delivered in the intervention (i.e. the ‘active ingredients to change behavior’ or behavior change techniques) and how the intervention was delivered (i.e. who delivered, to whom, how often, for how long, in what format, and in what context). Behavior change techniques were categorized using the taxonomy of Michie [12]. This taxonomy includes 93 Behavior Change Techniques, grouped into 16 categories; for example the categories feedback and monitoring, comparison of behavior, repetition and substitution. Moreover, contextual (e.g. characteristics of target participants who receive the interventions) characteristics of the parenting interventions will also be assessed.

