### Data management and statistical analysis

Data are handled according to the guidelines of the EU General Data Protection Regulation (GDPR). Data-management and analysis will be carried out at the Erasmus MC University Medical Center. Paper questionnaires will be transferred into electronic files and checked for missing or incorrect data. All data are handled confidentially and scientific data are stored anonymously.

Descriptive statistics will be used to describe the characteristics of the study population. We will use linear regression analysis for continuous outcome measures, and logistic regression analysis for dichotomous outcome variables. The exposure to (elements of) parenting interventions (yes/no) is the independent variable. In additional models, the baseline measurements and potential confounders (e.g. demographic characteristics of the caregivers and children) will be added. It will be evaluated whether additional multi-level regression analyses should be performed given the potential clustering within the youth health care organizations in the study. The exposure to parenting support will be based on information obtained from the follow-up questionnaire and when available the electronic files of the youth health care organizations. All analyses will be performed using SPSS version 24 for windows and R (version 3.4.1). Missing data will be handled by multiple imputation. All tests will be two-sided and *p*-values less than 0.05 will be considered as significant.

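### Exposure rests on caregiver recall in the same follow-up questionnaire as the outcomes, with files added only for some; a source-specific check is needed before elements are called effective

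*Protocol article*

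**What the plan says.** All references are to the protocol article.

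- **Informant.** Under Data collection and measurements: "Data will be collected through questionnaires that will be filled out by the primary caregiver of the child at baseline", and again at twelve months.
- **Outcomes.** Under Outcome measures, unless otherwise specified, "measures will be assessed at baseline as well as at follow-up". Parenting style, discipline, daily hassles, competence, family functioning, the CBCL and the sleep, eating and crying items are all caregiver ratings.
- **Exposure.** Under Received parenting support and use of care, the follow-up questionnaire asks about centre visits, interventions, lectures and more: "other types of parenting support during the last year are assessed by 20 items". These items also ask how the parent valued the support.
- **Files.** The same section adds a second source conditionally: "when available and with permission of participants, data on received parenting support and care regarding parenting during the follow-up period will be collected" from preventive youth health care organisations. The statistical section repeats the condition: "The exposure to parenting support will be based on information obtained from the follow-up questionnaire and when available the electronic files".
- **Elements.** To code elements, "we will inventory the guidelines and/or protocols of the interventions that were reported by the parents/caregivers".
- **Recruitment.** Part A (net 800) comes from two youth health care registries. Part B (net 200) comes through providers of parenting support, and in addition "participants are recruited directly through advertisements on websites about parenting".
- **Adjustment.** Baseline measurements and confounders enter in additional models.
- **Limitations.** The Discussion names hard-to-reach parents, residual confounding and unmeasured implementation quality. It does not name recall error, the shared informant or unequal ascertainment.

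**The concern.** Two features act together.

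First, one person supplies both sides of the regression at one sitting. If a caregiver's state at follow-up influences how fully she recalls support, errors in exposure and outcome are correlated. An association can then appear without any effect, or a real one can be hidden. Because elements are coded from the interventions that parents report, the error carries into the element-level results, which are the study's main target.

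Second, the main check on that error, the electronic files, is present for some participants and absent for others. Some parents are classified from two sources and others from recall alone. File coverage may differ between Part A and Part B, and Part B was chosen because its parents will take part in an intervention. Completeness of ascertainment may therefore be tied to exposure itself.

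The Discussion expects the results to show which elements are effective and to guide practice and policy. A reader of those results would have no way to tell a reporting artefact from an effect.

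**Working it through.** **1. The plan's own figure** (Power considerations: 600 completers, 300 per group, mean cluster size 24, ICC 0.02, two-sided 0.05, power 0.80).
- Design effect: 1 + (24 − 1) × 0.02 = 1.46.
- Effective n per group: 300 / 1.46 = 205.5.
- Detectable difference: (1.960 + 0.842) × √(2 / 205.5) = 0.276 SD.

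The stated 0.27 SD is reproduced closely (power at 0.27 is 78.1%). It assumes exposure is classified without error.

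**2. Outcome-dependent recall, no true effect, unadjusted.** Assumptions, none from the documents: a normal outcome, no false reports, and recall that differs between the worse and better halves of the follow-up outcome. The 50% truly exposed is the plan's figure. The two halves of a standard normal have means ±0.798, a gap of 1.596 SD.

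Recall 90% (worse half) and 70% (better half):
- Reported exposed: 0.25 × 0.9 + 0.25 × 0.7 = 0.225 + 0.175 = 0.40.
- Share from the worse half among reported exposed: 0.225 / 0.40 = 0.5625.
- The same share among reported unexposed: 0.275 / 0.60 = 0.4583.
- Spurious difference: (0.5625 − 0.4583) × 1.596 = 0.166 SD, or 0.166 / 0.276 = 60% of the detectable difference.

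Recall 90% and 80%:
- 0.225 / 0.425 − 0.275 / 0.575 = 0.5294 − 0.4783 = 0.0512.
- Spurious difference: 0.0512 × 1.596 = 0.082 SD, or 30% of 0.276.

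**3. The same scenarios with baseline outcome in the model.** If reporting depends only on the follow-up state, and baseline and follow-up correlate at r, the adjusted bias is about (1 − r²) times the crude bias. The documents give no r; 0.5 to 0.7 is assumed.

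| Recall | Unadjusted | r = 0.5 (× 0.75) | r = 0.7 (× 0.51) |
|---|---|---|---|
| 90% / 70% | 0.166 SD | 0.12 SD | 0.08 SD |
| 90% / 80% | 0.082 SD | 0.06 SD | 0.04 SD |

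The first row is then about 31% to 45% of 0.276 (0.085 / 0.276 and 0.125 / 0.276). Adjustment removes what is due to stable distress or reporting style. What is tied to the caregiver's state at follow-up remains.

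**4. A second error model, unadjusted.** Here false reports are allowed, and the odds of reporting support rise smoothly with a worse current outcome, by a factor of 1.22 to 2.01 per SD. Sensitivity runs from 0.70 to 0.90 and specificity from 0.90 to 0.95. Spurious differences run from 0.06 to 0.43 SD. With a factor of 1.0 (error unrelated to outcome) the spurious difference is zero.

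**5. Error unrelated to outcome still attenuates.** The factor is P(true | reported exposed) − P(true | reported unexposed).
- Sensitivity 0.90, specificity 0.95: 0.450 / 0.475 − 0.050 / 0.525 = 0.852, so 0.27 becomes 0.23 SD.
- 0.80 and 0.90: 0.400 / 0.450 − 0.100 / 0.550 = 0.707, so 0.19 SD.
- 0.70 and 0.90: 0.350 / 0.400 − 0.150 / 0.600 = 0.625, so 0.17 SD.

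**6. What a file-only analysis could resolve.** The linked share is not stated. Take 75%, 50% or 25% of 600, half exposed, spread evenly over the 25 clusters (18, 12 or 6 per cluster):
- 75%: design effect 1.34; 2.802 × √(2 / (225 / 1.34)) = 0.31 SD.
- 50%: design effect 1.22; 2.802 × √(2 / (150 / 1.22)) = 0.36 SD.
- 25%: design effect 1.10; 2.802 × √(2 / (75 / 1.10)) = 0.48 SD.

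The linked subset is useful as a check, but too imprecise for the sign of its estimate to decide a conclusion.

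**The case against.** The strongest reply has five parts.

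- **No merging rule is stated.** The article names the two sources but not how they are combined, and it does not exclude source-specific analyses. A condensed article may leave that to a fuller plan. This stands: the absent rule is not the point. The point is the stated reliance on recall supplemented unevenly, and a limitations list that omits it.
- **Outcome-dependent recall is assumed.** This stands. Nothing in the documents gives recall accuracy or links it to distress. A reader might infer that the design does create false associations; the documents support only that it can. The direction is open too. Fuller recall by strained parents makes support look harmful or hides benefit, which runs against the study hypothesis. Recall driven by satisfaction would flatter support.
- **Baseline adjustment is planned.** This stands in part. It reduces the illustrated bias by a quarter to a half, but does not remove it.
- **Using two sources is a recognised guard against under-reporting.** This stands. Moving the main analysis to questionnaire data alone would rest it wholly on the shared rater. With 40% drop-out expected, it would also set aside file data on parents who return no follow-up questionnaire. For Part B parents recruited through providers, the recruitment route also carries some information on exposure that is not recall.
- **Files cannot see everything.** This stands. The study covers books, websites and support from other providers. Requiring a file-based estimate in the same direction could not be met for support that the files never record.

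**Conclusion.** The concern holds in a limited form. The documents establish a shared informant for outcomes and recalled exposure, file data that depend on availability and permission, element coding that starts from parents' reports, and no mention of any of this among the limitations. It follows that ascertainment is unequal and that outcome-dependent recall can create or mask associations.

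The size rests on assumptions. With 90% versus 70% recall and no true effect, the bias is about 0.17 SD unadjusted, and 0.08 to 0.12 SD after baseline adjustment at r of 0.5 to 0.7. At 90% versus 80% it is about 0.08 SD and 0.04 to 0.06 SD. The detectable difference is 0.27 SD for an unadjusted comparison. Unequal file coverage by Part A and B is plausible from the recruitment routes, but no coverage figure is given.

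A reader might go further and infer that the planned exposure variable is invalid, or that the files should be kept out of the main analysis. The documents support neither. What is missing is a check, which the data already to be collected allow.

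**What to change.** Keep the planned exposure definition for the main models. Add the following to Data management and statistical analysis:

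1. In participants with linked files, repeat the models for the second study question twice: once with file-recorded exposure alone and once with questionnaire exposure alone. Limit both to types of support that the files can record.
2. Report agreement between questionnaire and file by outcome level, for example PDH or CBCL score above versus below the median.
3. Report file availability separately for Part A and Part B.
4. Where the two source-specific estimates clearly disagree, do not describe that element as effective without stating the disagreement.

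Add shared-rater and recall error, and unequal ascertainment, to the limitations in the Discussion.

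**Cost.** No new data collection, since the files are already to be extracted; one extra analysis set and a few sentences. The file-only estimate uses a smaller subset and covers only support recorded by youth health care organisations, so it serves as a check and not as a veto.

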### Power considerations

In total, we aim to include net 1000 parents/caregivers in the study. With an expected 40% loss to drop-out between baseline and follow-up, we expect complete data of *n* = 600 participants. We assume that 50% (300) of these parents/caregivers will have received parenting support during the follow-up period. We assume an alpha of 0.05 (2-tailed) and power of 0.80. We apply a correction factor to account for the cluster design, assuming 25 clusters within the sample with an average cluster size of 24 participants and an intra-class correlation coefficient of 0.02. For this expected sample size and assumptions, with regard to the continuous outcome measures, a difference of 0.27 SD (standard deviation) between the subgroup exposed to parenting support and the subgroup not exposed to parenting support can be detected at follow-up. This is enough to indicate relevant effects, as a difference of 0.5 SD is considered meaningful [41, 42].

## Discussion

This article describes the study protocol of a prospective cohort study that is part of the CIKEO consortium study (Consortium Integration Knowledge promotion Effectiveness Of parenting interventions). The overarching aim of the CIKEO consortium is to investigate preventive parenting interventions, in order to identify effective elements within these interventions. The aim of the prospective cohort study is to investigate the exposure of parents/caregivers to parenting support elements and strategies in daily practice of Dutch preventive youth health care and the effects of this exposure on parenting skills, family functioning and child development in a naturalistic effect evaluation. We hypothesize that parents/caregivers who have been exposed to elements of parenting support during the follow-up period will show significant improvements in specific outcome variables related to parenting skills, family functioning and child development when compared to comparable parents/children who not have been exposed to parenting interventions.

This study has several strengths. First, the data are collected in a naturalistic setting, as the cohort study is conducted in the setting of daily youth health care practice. This enables us to explore the effects of parenting interventions in the “real world” rather than in an experimental setting, which will support the generalizability of our findings [19]. Furthermore, we will not only examine the effects of parenting interventions but also the effects of other types of parenting support provided by preventive youth health care. These types of parenting support are important to take into account, as previous research has indicated that such parenting support can also have relevant effects [43].

The proposed study also has some limitations and we expect to encounter some challenges. The first challenge of this study will be to include parents at risk of parenting problems. It may be a difficult group to reach, and these parents may be hesitant to participate in research [44]. To increase participation, we will recruit these parents through providers of parenting support. Second, because of the non-randomized design, results of the study are subject to confounding variables. We will assess the most important confounding variables; however, there may be residual confounding. Another limitation is that it is not possible to evaluate some general elements that have been shown to be of importance to the effectiveness of parenting interventions in our study design, such as the quality of the implementation of the interventions [7]. Although we cannot include it in our study, we know that these factors may be important to take into account and we emphasize the need to investigate these factors more thoroughly in future studies.

In conclusion, results of the naturalistic effect evaluation study will provide insight in which parenting support elements and strategies are used in daily practice, and which elements are effective. The results will be translated into products for practice and education; recommendations for practice and policy will also be made. The knowledge provided by CIKEO is valuable for various stakeholders in practice, including providers of parenting support (youth health care organizations and parent training institutes) and municipalities that provide interventions. It will enable professionals and policy makers to concentrate on elements of parenting support that are shown to be effective and to adapt parenting support to better fit the needs of clients and the possibilities within organizations and local settings. Furthermore, it may guide the future development and improvement of interventions. Ultimately, the goal is to make parenting support more flexible and more effective.

